## Abstract

**Background:**

Cardiac toxicity due to ingestion of oleander plant seeds in Sri Lanka and some other South Asian countries is very common. At present symptomatic oleander seed poisoning carries a mortality of 10% in Sri Lanka and treatment of yellow oleander poisoning is limited to gastric decontamination and atropine administration. The only proven effective antidote is digoxin antibodies but these are not available for routine use because of the high cost. The main objective of this study is to investigate the effectiveness of a new and inexpensive antidote for patients with life threatening arrhythmias due oleander poisoning.

**Method/design:**

We set up a randomised double blind clinical trial to assess the effectiveness of Fructose 1, 6 diphosphate (FDP) in acute yellow oleander poisoning patients admitted to the adult medical wards of a tertiary hospital in Sri Lanka. Patients will be initially resuscitated following the national guidelines and eligible patients will be randomised to receive either FDP or an equal amount of normal saline. The primary outcome measure for this study is the sustained reversion to sinus rhythm with a heart rate greater than 50/min within 2 hours of completion of FDP/placebo bolus. Secondary outcomes include death, reversal of hyperkalaemia on the 6, 12, 18 and 24 hour samples and maintenance of sinus rhythm on the holter monitor. Analysis will be on intention-to-treat.

**Discussion:**

This trial will provide information on the effectiveness of FDP in yellow oleander poisoning. If FDP is effective in cardiac glycoside toxicity, it would provide substantial benefit to the patients in rural Asia. The drug is inexpensive and thus could be made available at primary care hospitals if proven to be effective.

**Trial Registration:**

Current Controlled trial ISRCTN71018309

## Background

Cardiac glycoside toxicity is the most common type of plant poisoning in Sri Lanka and some other South Asian countries [1-3]. At present, symptomatic cardiac glycoside poisoning carries a mortality rate of 10% in Sri Lanka [1]. Cardiac glycosides inhibit the enzyme Na-K-ATPase of the cardiac myocyte and the conducting system and increase intracellular calcium concentrations. This rise in intracellular calcium may be a mechanism for ventricular arrhythmias [4]. These effects lead to increased automaticity and excitability both during early and late depolarization of the cardiac cell. Patients also develop very high serum potassium concentrations as a result of inhibition of Na-K-ATPase. Patients may develop arrhythmias and become hypotensive. Hypotension interferes with intracellular production of ATP through glycolysis, as lactate (produced due to anaerobic metabolism) inhibits the rate limiting enzyme phosphofructokinase. This in turn will further reduce the activity of Na-K-ATPase resulting in a vicious cycle.

FDP (CAS registry number 488-69-7; Merck monograph number 4297) is a phosphorylated sugar that is a normal physiological intermediary in glycolysis. It is produced from glucose by the action of phosphofructokinase during glycolysis and is in turn broken down into pyruvate. Phosphofructokinase activity is the main rate-limiting factor for ATP production from glucose under anaerobic conditions. Given intravenously, FDP is capable of being actively transported into cells and acting as an alternative energy source to glucose [5]. This can increase ATP production in circumstances where phosphofructokinase is inhibited (for example by lactate). The relative production of ATP is greater for FDP than glucose.

FDP has also been shown to stimulate Na-K-ATPase activity, and inhibit potassium efflux from myocardial cells [6,7]. It is hypothesised that these mechanisms may contribute to its activity in cardiac glycoside poisoning where Na-K-ATPase is inhibited and extracellular potassium is high. FDP also chelates ionised calcium. A decrease in ionised serum calcium and/or cardiac uptake of calcium may also be favourable,[8] given the high intracellular calcium that occurs in cardiac glycoside poisoning.

These theoretical benefits of FDP have been shown in an animal study done at the Mississippi School of Medicine, USA. This study showed evidence of effectiveness of FDP in dogs poisoned with a relative of the yellow oleander - the common or pink oleander. Cardiac arrhythmias in dogs (6/6;100%) treated with FDP (50mg/kg IV) reverted back to sinus rhythm within 30 minutes while the arrhythmias in the control animals killed one animal and did not revert over four hours in the other five at which time they were sacrificed [7]. There was also no rise in serum potassium in the group receiving FDP while marked hyperkalemia occurred in the control group [7].

We conducted a small phase II study of increasing IV bolus doses (30 to 250mg/kg) of FDP in patients with yellow oleander poisoning in Sri Lanka in 2006-7. The aim of that study was to find a safe dose of FDP that might be used to reverse cardio-toxicity. The agent was well tolerated with no evidence of any adverse effects attributable to FDP at any of the doses and an apparent reduction of around 0.5 mmol/L of potassium and 0.3mmol/L of calcium in the highest FDP dose group. All these doses were well within the range of doses used in previous human studies for other conditions [9].

### Previous Human Experience/safety profile for other indications

FDP has a well established safety profile in humans. It has been administered as a component of total parenteral nutrition (TPN) and has been used short-term in numerous experimental human studies. It has generally been shown to have favourable effects in these studies. For example, in individuals with coronary artery disease and heart failure, IV FDP increased cardiac work and reduced ventricular filling pressures [10].

The minimum dose where effects have been seen is around 25-50mg/kg [10]. Doses up to 250mg/kg IV have been used safely as a single dose [10-13] and 750 mg/kg IV as a cumulative dose (over 12 hours) [12]. The most pivotal study was a dose-ranging study of FDP to reduce ischemic injury post coronary artery bypass grafting. Five doses between 50mg/kg and 750 mg/kg in divided doses were tested with the optimal dose being 250mg/kg IV given over 30 minutes [12].

FDP is an approved product in Italy - the only safety concerns identified in the product information are a very rare risk of hypersensitivity reactions [14]. The approved dose range in Italy covers the doses to be used in this study.

## Methods/Design

### Design

The study is a double blind randomised controlled clinical trial with two parallel groups. The trials is designed to be compliant with the CONSORT Statement [15]

### Patients

All patients who present with a history of yellow oleander poisoning will be assessed to determine if they are eligible for the study. Those who meet the criteria will be approached to give their written informed consent, following which they will be randomised (Figure 1). Patients who do not initially meet the criteria will be reviewed regularly and approached if they meet the inclusion criteria at a later time point.

**Figure 1 F1:**
[figure not shown]
**Trial profile**.

#### Inclusion criteria

patients who are admitted to adult medical wards, who are over the age of 16years, and who have any of the following manifestations of oleander induced cardiac toxicity:

• 2^nd ^degree heart block

• 3^rd ^Degree heart block

• Bradycardia with a heart rate of less than 40 beats/minute

• Any rhythm with a systolic blood pressure below 80 mm Hg

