### Randomisation

Randomisation is done using purpose designed computer software. The random sequence and allocation are concealed prior to randomisation. The program will randomise eligible patients in a 1:1 ratio. The allocation sequences are generated and encrypted independently by an IT consultant who has no role in patient recruitment, treatment and assessment.

The randomization will be performed by study pharmacists centrally. If a patient meets the inclusion criteria and gives consent, clinical research assistants will call the pharmacist with details such as name, hospital number and weight of the patients. Then the pharmacist will randomise the patients and prepare the placebo or active treatments for the study team. The allocation will only be known by the pharmacists who will have no other role in patient management and data collection. Intention-to-Treat analysis will be applied. That is, the analysis will include all randomised patients in the groups to which they were assigned, regardless of non-compliance, protocol deviations, withdrawal, and anything that happens thereafter [17]

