### Outcomes

The primary outcome of this study is the reversion to sustained sinus rhythm with a heart rate >50 bpm within 2 hours of completion of bolus.

Secondary outcomes include:

1. Death

2. Change from baseline serum potassium on the 6, 12, 18 and 24 hour blood samples.

3. Time to revert and duration of reversion to sinus rhythm on the Holter monitor over the first 24 hours (reflecting the efficacy of bolus and infusion)

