### Sample size

We are planning to recruit 240 symptomatic patients with yellow oleander poisoning admitted to Teaching Hospital, Kurunegala and National Hospital Sri Lanka, Colombo. In the study by Eddleston M et al [18], 2/32 (6.25%, 95% CI 1% - 19%) patients reverted to sinus rhythm spontaneously after 2 hours. Second degree and third degree heart block are markers of toxicity but may not be strong predictors of death (which may be due to myocardial toxicity rather than atrio-ventricular conduction block). Reversion to sinus rhythm is more likely with less severe second degree block. We would ideally have a sample size that ensured a significant number of third degree blocks which are less likely to revert spontaneously so that the effect of treatment in this sub-group can be seen. However, the proportions of the different grades of block are not well quantified and thus precise estimates of power in sub-groups are not possible.

We expect up to 15% spontaneous reversion by two hours and believe a 40% reversion in the active treatment arm would be clinically significant and likely to provide strong evidence that this would translate to a mortality benefit. This would require just 60 patients in each arm (α = 0.05, β = 0.8, missing data/dropout 10%). To increase the likelihood of recruiting enough patients with 3^rd ^degree heart block to see if the effect is observed in the most severely poisoned patients, and to account for possible differences between centres we intend to do a study of 120 patients in each arm.

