### Study hypothesis and principal comparisons

The primary outcome of the study is to investigate if the addition of FDP (250mg/kg loading dose over 20 minutes followed by 6mg/kg/hr for 24 hours) to routine treatment will completely reverse serious arrhythmias within two hours. The study will also investigate the effect of FDP on the presence of abnormal rhythms and serum potassium and other electrolytes over 24 hours.

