### Statistical Analysis

The Primary outcome (proportion with reversion to sinus rhythm) will be compared with the chi-squared test. Kaplan Meier curves will be constructed to demonstrate the cumulative reversion to sinus rhythm over time. A Cox proportional hazard model will be used to test the overall difference in reversion to sinus rhythm between treatments adjusted for baseline variables as necessary. A longitudinal statistical technique known as Generalised Estimating Equation (GEE) will be used to analyze changes in electrolytes (e.g. potassium) over time.

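### Patients enrolled for low blood pressure in any rhythm may already be in sinus rhythm above 50 bpm, so the primary outcome of reversion is undefined for them and the planned effect is diluted

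*Protocol article*

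**What the plan says.** Under Inclusion criteria, the protocol article enrols adults "who have any of the following manifestations of oleander induced cardiac toxicity". One item on the list is therefore enough. Three items are defined by rhythm or rate: second-degree block, third-degree block, and a rate under 40. The fourth is "Any rhythm with a systolic blood pressure below 80 mm Hg". The Exclusion criteria do not remove patients in sinus rhythm.

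Under Outcomes, the primary outcome is "the reversion to sustained sinus rhythm with a heart rate >50 bpm within 2 hours of completion of bolus". Study hypothesis and principal comparisons gives the aim as finding out whether FDP "will completely reverse serious arrhythmias within two hours".

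The analysis population is fixed under Randomisation: "the analysis will include all randomised patients in the groups to which they were assigned". Under Statistical Analysis, "The Primary outcome (proportion with reversion to sinus rhythm) will be compared with the chi-squared test".

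The Sample size section plans on reversion alone: "We expect up to 15% spontaneous reversion by two hours and believe a 40% reversion in the active treatment arm would be clinically significant". It discusses grades of heart block and does not mention patients enrolled on blood pressure only.

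**The concern.** Eligibility, outcome and analysis population are each stated clearly, but they do not fit together. A patient enrolled only for low systolic pressure may be in sinus rhythm above 50 bpm at entry. Such a patient stays in the denominator of the chi-squared test, yet reversion has no meaning for them. Someone must decide whether they count as successes or failures, and the two choices give different results.

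Three things are at stake.

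- **The effect estimate.** Patients who score alike in both arms pull the risk difference towards zero.
- **The control rate.** If they count as successes, the control proportion mixes spontaneous reversion with patients who never had an arrhythmia. It can no longer be compared with the 15% in the plan.
- **The other analyses of the same event.** Time to reversion, the Kaplan-Meier curves and the Cox model have a time of zero or no defined time for these patients. The interim look examines the same primary outcome.

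**Working it through.** **Inputs.** From Sample size: 15% v 40%, α = 0.05 (two-sided assumed), the stated β = 0.8 read as 80% power, 10% dropout, 60 per arm required, 120 per arm planned. From the IDMEC section: 15% v 60% (reading the 60% effect as a 60% response), α = 0.001, 60 per arm. Assumed, because the article does not give it: f, the share of patients already in sinus rhythm above 50 bpm at randomisation.

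**Step 1: the plan's own figure.** With the mean proportion 0.275:

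n = [1.960 √(2 × 0.275 × 0.725) + 0.842 √(0.15 × 0.85 + 0.40 × 0.60)]² / 0.25² = 48.9, so 49 per arm, and 49 / 0.9 gives 55.

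With a continuity correction, n is 57, and 57 / 0.9 gives 64. The stated 60 lies between the two. With 60 × 0.9 = 54 evaluable per arm, exact power is 84% for the uncorrected chi-squared test and 79% for the Yates or Fisher version. The figure of 60 is sound for its stated rates. The planned 120 per arm leaves 120 × 0.9 = 108 evaluable.

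**Step 2: dilution.** Suppose the share f has the same result c in both arms (c = 1 success, c = 0 failure). Then

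p(arm) = (1 − f) × p + f × c, and the difference = (1 − f) × (0.40 − 0.15) = 25 × (1 − f) points for either c.

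Example, f = 20%. As successes: 0.8 × 0.15 + 0.2 = 32% v 0.8 × 0.40 + 0.2 = 52%. As failures: 12% v 32%. Both differ by 20 points.

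**Step 3: power at the planned size.** Exact binomial power of the two-sided uncorrected chi-squared test with 108 evaluable per arm. The last column drops the share f and keeps 15% v 40% in 108 × (1 − f) per arm.

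| f | Difference (points) | As successes: rates, power | As failures: rates, power | Only patients who can revert: n per arm, power |
|---|---|---|---|---|
| 0% | 25.0 | 15% v 40%, 99% | 15% v 40%, 99% | 108, 99% |
| 10% | 22.5 | 23.5% v 46%, 94% | 13.5% v 36%, 98% | 97, 98% |
| 20% | 20.0 | 32% v 52%, 85% | 12% v 32%, 95% | 86, 96.5% |
| 30% | 17.5 | 40.5% v 58%, 73% | 10.5% v 28%, 92% | 76, 94% |

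Power reaches the stated 80% at f of about 24% if these patients count as successes. If they count as failures, it does so only well above 40% (about 46% by normal approximation).

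**Step 4: interim look.** The design reproduces: 15% v 60% at α = 0.001 and 95% power needs 53 per arm, and 53 / 0.9 gives 59 against the stated 60. With 54 evaluable per arm, exact power is 96% at f = 0. It falls to 85% (successes) or 91% (failures) at f = 10%, and to 68% or 82% at f = 20%. Restricting to patients who can revert gives 93% at f = 10% (49 per arm) and 89% at f = 20% (43 per arm).

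**The case against.** **Unknown share.** The article gives no value for f. It describes the target patients as having life-threatening arrhythmias, so a small f fits the text at least as well as a large one. This stands: every power figure above with f greater than 0 rests on an assumption.

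**Underpowered?** A reader might infer that the trial falls below its planned power. The documents do not support that. The final sample is 120 per arm, not 60, and at that size power stays above 80% up to f of about 24% even under the worse scoring. The extra patients were added for third-degree block and centre differences, so the margin was meant for another purpose, but the overall test still has it.

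**Met or impossible at entry?** A reader might also infer that these patients automatically succeed or fail and tell us nothing. That is too strong. The rhythm must be sustained, and the article itself expects some patients to become eligible later and some arrhythmias to recur. A hypotensive patient in sinus rhythm could deteriorate within two hours, and treatment might affect that. Any contrast so produced would be maintenance of rhythm, not reversion.

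**Literal scoring.** Read literally, a patient with nothing to revert does not meet the outcome. Under that scoring, restricting the analysis gains little power: about 1 point at f = 20% and 3 at f = 30%. This is fair, but the article does not state the rule, and the estimate is diluted by the same amount either way.

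**Article format.** Scoring rules for unusual cases often sit in the full protocol or the analysis plan, neither of which is shown. That answers a complaint that something is missing. It does not remove the conflict between an entry criterion, an outcome and an analysis population that the article does state.

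**Conclusion.** The mismatch is real and nothing in the article resolves it. The result of a patient already in sinus rhythm above 50 bpm at randomisation is undefined as reversion, and this holds whatever f is. If such patients score alike in both arms, the planned 25-point difference shrinks to 25 × (1 − f). If they count as successes, the control rate loses its meaning as spontaneous reversion. Interim power also falls, from 96% to 85% or 91% at f = 10%.

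The loss of power in the final test is modest for moderate f, and no shortfall against the stated 80% is shown. These sizes assume equal scoring in both arms, 10% dropout, a two-sided uncorrected chi-squared test, and planning rates that hold in patients who can revert. The point deserves a clear amendment; it does not invalidate the design.

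**What to change.** Before unblinding, and before the 120-patient interim look:

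1. Define the primary analysis set as all randomised patients whose last ECG before randomisation was not sinus rhythm above 50 bpm, analysed in the groups assigned. This is a baseline attribute, so the randomised comparison is preserved. Amend the intention-to-treat statement to match.
2. Use the same set for time to reversion, the Kaplan-Meier curves and the Cox model.
3. Keep all randomised patients for death and potassium.
4. Report the all-randomised primary result as a sensitivity analysis, with the scoring of the remaining patients stated in advance.

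Eligibility and treatment do not change. The cost is a primary set smaller than 240 by the share f: 216 at f = 10%, 192 at f = 20%, 168 at f = 30%, before dropout. In every case computed, the restricted analysis had at least as much power as the all-randomised test, although the interim look does not regain its full 96%.

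Recovery of systolic pressure could be reported as an optional extra, since blood pressure is already monitored for 24 hours. Its absence from the outcomes is not an error.

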#### Exclusion criteria

Patients with documented ischemic or valvular heart disease, pregnant women and age under 16 years.

### Patient management

Standard oleander patient management guidelines will be followed. These are based on the national poisoning treatment guidelines[16]. The only difference between enrolled patients and those not enrolled will be the addition of FDP/placebo intervention.

### Trial intervention and study procedures

Patients randomised to the treatment arm will be treated with 250mg/kg loading dose of FDP (Esafosfina from Biomedical Foscama, Italy) over 20minutes followed by 6mg/kg/hr for 24 hours in addition to standard care. Patients randomised into the control arm will be treated with an equal volume (equal to the volume of FDP in the treatment arm) of 0.9% saline as a bolus and a 24 hour infusion. All attending doctors and nurses will be blinded to the treatment.

Clinical parameters such as systolic and diastolic blood pressure will be monitored for 24 hours. A Holter monitor will record the cardiac rhythm for 48 hours. All cardiac events will be recorded. If a serious cardiac rhythm abnormality recurs after an initial response to the bolus (within 2 hours of a bolus), a further bolus of 250mg/Kg of FDP (or equal volume of placebo) may be given at the discretion of the treating physician while the infusion will be maintained at the same rate.

### Randomisation

Randomisation is done using purpose designed computer software. The random sequence and allocation are concealed prior to randomisation. The program will randomise eligible patients in a 1:1 ratio. The allocation sequences are generated and encrypted independently by an IT consultant who has no role in patient recruitment, treatment and assessment.

The randomization will be performed by study pharmacists centrally. If a patient meets the inclusion criteria and gives consent, clinical research assistants will call the pharmacist with details such as name, hospital number and weight of the patients. Then the pharmacist will randomise the patients and prepare the placebo or active treatments for the study team. The allocation will only be known by the pharmacists who will have no other role in patient management and data collection. Intention-to-Treat analysis will be applied. That is, the analysis will include all randomised patients in the groups to which they were assigned, regardless of non-compliance, protocol deviations, withdrawal, and anything that happens thereafter [17]

### Outcomes

The primary outcome of this study is the reversion to sustained sinus rhythm with a heart rate >50 bpm within 2 hours of completion of bolus.

Secondary outcomes include:

1. Death

2. Change from baseline serum potassium on the 6, 12, 18 and 24 hour blood samples.

3. Time to revert and duration of reversion to sinus rhythm on the Holter monitor over the first 24 hours (reflecting the efficacy of bolus and infusion)

### Sample size

We are planning to recruit 240 symptomatic patients with yellow oleander poisoning admitted to Teaching Hospital, Kurunegala and National Hospital Sri Lanka, Colombo. In the study by Eddleston M et al [18], 2/32 (6.25%, 95% CI 1% - 19%) patients reverted to sinus rhythm spontaneously after 2 hours. Second degree and third degree heart block are markers of toxicity but may not be strong predictors of death (which may be due to myocardial toxicity rather than atrio-ventricular conduction block). Reversion to sinus rhythm is more likely with less severe second degree block. We would ideally have a sample size that ensured a significant number of third degree blocks which are less likely to revert spontaneously so that the effect of treatment in this sub-group can be seen. However, the proportions of the different grades of block are not well quantified and thus precise estimates of power in sub-groups are not possible.

We expect up to 15% spontaneous reversion by two hours and believe a 40% reversion in the active treatment arm would be clinically significant and likely to provide strong evidence that this would translate to a mortality benefit. This would require just 60 patients in each arm (α = 0.05, β = 0.8, missing data/dropout 10%). To increase the likelihood of recruiting enough patients with 3^rd ^degree heart block to see if the effect is observed in the most severely poisoned patients, and to account for possible differences between centres we intend to do a study of 120 patients in each arm.

